### Collection and Management of Data

According to the requirements of Good Clinical Practice and our research plan, the investigator shall input data to eCRFs accurately, completely, normatively, and in a timely fashion based on the original observations of participants. To ensure the accuracy of the data, two personnel specializing in data entry should undertake double-entry and proofreading independently. The auditor shall monitor whether the research is conducted following the research plan, ascertain whether all eCRFs have been completed correctly and are consistent with the original data, and issue questions at any time in case of any problem. If errors and omissions are made, the researcher shall be corrected promptly.

After inspection by the auditor, eCRFs must be transmitted to the department of data management in time. In this study, data management will be carried out with an electronic data-capture system by the Department of Medical Statistics within the First Hospital of Peking University (Beijing, China). The data administrator shall adopt system-automatic and manual-logic verification to check the consistency of eCRF data and source data. For questions in the eCRFs, the data administrator will generate a question–answer form and send an inquiry to the investigator through the clinical monitor. The investigator should answer the question as soon as possible, and the data administrator will modify the data according to the investigator's answer. If necessary, a question–answer form can be issued again. After being reviewed and confirmed by the primary researcher, sponsor, statistical analyst, and data administrator, the data will be locked and submitted to the statistician for analyses.

Personal information about potential and enrolled participants will be protected confidentially throughout the trial, and researchers should maintain data secrecy for five years after termination of the trial.

### Sample Size

The formula for calculating the sample size is based on the superior clinical trial sample size estimation (Wan et al., 2017). The sample size is driven by the expected improvement in 6MWD. Referring to clinical studies (Fan and Zhang, 2012; Guo and Li, 2013; Du, 2014; Wu et al., 2015), we assumed that the improvement in 6MWD is 30 m, and the combined standard deviation (SD) is 100 m in the present study. Given a rate of type-I error of *α* = 0.025, a power of 80% (rate of type-II error of *β* = 0.2), and, considering a possible dropout rate of 20%, 470 patients will need to be allocated. For the convenience of randomization, the final sample size was 320 cases in the intervention group and 160 cases in the placebo group, a total of 480 cases.$$n_{1}={\left[\frac{\left({µ}_{\alpha }+{µ}_{\beta }\right)\sigma }{\delta }\right]}^{2}\frac{\left(1+k\right)}{k},\;n_{2}=k\;n_{1}.$$

In this formula, *k* is the ratio between two sample cases, *δ* is the expected improvement in 6MWD, and *σ* is the combined SD.

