### Randomization, Allocation Concealment Mechanism, and Blinding

Participants will be randomized to the GXST group or placebo group in a 2:1 ratio using the Central Randomization System to achieve computerized randomization in blocks of six, stratified by center. The random sequence will be retained in an envelope and sealed subsequently. According to the randomization number, a statistician will send the envelope directly to Shaanxi Buchang Pharmaceutical Co., Ltd. for labeling of the intervention drug and placebo drug. All researchers, participants, physicians, drug administrators, and dispensing nurses will be blinded to the type of treatment until the study is completed. Unblinding will be available if participants experience an SAE or need to be rescued in an emergency situation. Once unblinded, the participant will withdraw from the study. Researchers should report the reasons to the inspector within 24 h. The precise cause of unblinding, date of the AE, the treatment situation, and the results must be recorded in eCRFs.

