### Statistical Analyses

The statistical analysis plan will be specified before data analyses. The statistical analyses will be undertaken *via* Statistical Analysis System v9.4 (or higher version) by the Department of Medical Statistics, Peking University First Hospital. Professional statisticians who are independent of all other processes of our study will carry out analyses. Consistent with the CONSORT statement and ITT principle, and the last observation, carried forward method will be used for missing values. Cases in the per protocol set (PPS) will be those who adhere to the protocol closely without the absence of baseline characteristics. Analyses of primary outcome and curative effect will be carried out using a full-analysis-set approach and PPS approach. The safety analysis set will include all randomized patients who have accomplished at least one study visit. Participating centers will be required to sum-up participant numbers in each center and list participants who have been removed from PPS.

For continuous variables, we will calculate the mean, SD, median, minimum, maximum, and interquartile range. For categorical variables, we will describe various frequencies or percentages. The chi-square test or Fisher's exact test will be used for categorical variables. The Student's *t*-test will be used for continuous variables with a normal distribution. For data that do not have a normal distribution, intragroup or intergroup differences before and after treatment will be analyzed by the Wilcoxon rank-sum test. The proportion of patients with AEs in two groups will be compared using the chi-square test or Fisher's exact test. Because patients who had use of ARNIs before the recruitment may constitute a specific population, we will run sensitivity analyses of the outcomes with patients used ARNIs as basic treatment, and adjusted for the effect of ARNIs. Significance will be assumed at a two-sided *p*-value less than 5%. The relative risk with corresponding 95% confidence interval to compare dichotomous variables will be calculated. Table 6 shows the method of analysis for specific outcomes.

**TABLE 6 T6:** Outcomes and methods of analyses.

Outcome/variable	Hypothesis	Measures	Methods of analyses
Baseline balance test			
		Quantitative outcomes (age, temperature, heart rate, respiratory rate, and blood pressure)	*t*-test/Wilcoxon rank-sum test

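### The stated 470 does not follow from the plan's own inputs: a 20% dropout rate needs 492 randomised, and the final 480 gives about 79% power at that loss (minor)

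*Protocol article*

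**What the plan says.** The Sample Size section bases the calculation on 6-minute walk distance (6MWD). It states the effect as "we assumed that the improvement in 6MWD is 30 m" and the variability as "the combined standard deviation (SD) is 100 m in the present study". It gives a "rate of type-I error of *α* = 0.025" and 80% power, and prints the usual formula for comparing two means with unequal allocation. It then concludes that, "considering a possible dropout rate of 20%, 470 patients will need to be allocated". For ease of randomisation this is raised: "the final sample size was 320 cases in the intervention group and 160 cases in the placebo group, a total of 480 cases".

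The section prints neither the evaluable number before the dropout allowance nor the step that turns it into 470.

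Three other places bear on the point:
- The section on randomisation fixes the ratio: "Participants will be randomized to the GXST group or placebo group in a 2:1 ratio".
- The Statistical Analyses section tests at a two-sided 5% level, and for incomplete data says that the last observation "carried forward method will be used for missing values".
- Table 6 lists a t-test or Wilcoxon rank-sum test for 6MWD, and also a covariance analysis.

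**The concern.** A dropout allowance should ensure that the required number is still there after the losses. For a loss of 20% the evaluable number is divided by 0.8. Multiplying it by 1.2 gives too few, because 20% of the enlarged total is more than 20% of the evaluable number. The stated 470 looks like the result of multiplying.

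The stated power, dropout rate and sample size would then not fit together in the paragraph that justifies the trial's size. The rounding to 480 might or might not make up the difference, so that has to be checked too.

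**Working it through.** **Inputs.** From Sample Size: δ = 30 m, σ = 100 m, α = 0.025, power 80%, dropout 20%. From the randomisation section: k = 2. I read α = 0.025 as one-sided, which matches the two-sided 5% test in Statistical Analyses (z = 1.960; z for 80% power = 0.8416). I read 30 m as the between-group difference in change, as the formula requires.

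**Step 1. Evaluable number, by the printed formula.**
- [(1.960 + 0.8416) × 100 / 30]² = 87.21
- n₁ (placebo) = 87.21 × (1 + 2)/2 = 130.8
- n₂ (GXST) = 2 × 130.8 = 261.6
- Total 392.4; rounded up by arm, 131 + 262 = 393

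**Step 2. Reproducing 470.**
- 392.4 × 1.2 = 470.9 (470.4 with z values cut to 1.96 and 0.84). This matches 470.
- 392.4 / 0.8 = 490.6. This does not.

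Other readings were tried:

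| Reading | Total |
|---|---|
| α = 0.025 two-sided, no dropout allowance | 475 to 477 |
| α = 0.025 two-sided, divided by 0.8 | 594 to 597 |
| α = 0.05 one-sided, divided by 0.8 | 386 to 390 |
| 1:1 allocation, α = 0.025 one-sided, × 1.2 or / 0.8 | 419 or 436 |

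Only the first row comes near 470. It ignores the 20% allowance that the text says was made, and it does not fit the two-sided 5% test.

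**Step 3. The allowance done correctly.**
- 393 / 0.8 = 491.25, so 492, which splits 2:1 as 328 + 164.
- 491 would not do: 491 × 0.8 = 392.8, below 393.

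**Step 4. What 470 and 480 give.** Power = Φ(δ / (σ√(1/n₁ + 1/n₂)) − 1.960), with 20% lost from each arm.

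| Randomised | Evaluable after 20% loss | Power (normal) | Power (exact t) |
|---|---|---|---|
| 470 | 376 | 78.3% | 78.1% |
| 480 | 384 (256 + 128) | 79.1% | 78.9% |
| 492 | 393.6 | 80.1% | 79.9% |

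For 480: √(1/128 + 1/256) = 0.10825, the standard error is 10.825 m, 30/10.825 = 2.771, 2.771 − 1.960 = 0.811, and Φ(0.811) = 0.791.

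**Step 5. The loss that each size can bear.**
- 480: 1 − 393/480 = 18.1%
- 470: 1 − 393/470 = 16.4%

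With no loss at all, 480 gives about 87%.

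**The case against.** **The multiplication is not printed.** This is correct. A reader might infer that the article documents the use of 1.2. It does not, and 470.9 is not exactly 470. The error does not depend on the route, however: 470 less 20% is 376, and the formula asks for 393.

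**Dropout is not the same as a missing primary outcome.** The section on withdrawal and dropout counts anyone who does not complete the observational period, whenever that happens. If the period means the full 52 weeks, patients lost after week 12 still have a primary outcome. At 480, a 20% rate is 96 patients and 480 − 393 = 87 can be lost, so 9 of the 96 leaving after week 12 would close the gap. This stands as a reason why actual power may reach 80%. It does not make 470 follow from a 20% allowance.

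**A covariance analysis is also listed.** Suppose that 100 m is the SD of change and the variance is the same at both visits. With baseline-to-week-12 correlation ρ, adjustment multiplies the variance by (1 + ρ)/2. At ρ = 0.8 the SD falls to 100 × √0.9 = 94.9 m, and power with 384 evaluable is about 83%. This could also close the gap. But the article says only that the SD is combined, not that it is the SD of change, and Table 6 does not say which 6MWD analysis decides the trial.

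**The full analysis set keeps dropouts in through carry-forward.** This does not restore the stated power. Table 5 schedules 6MWD only at baseline and week 12, so a patient lost before week 12 has only the baseline value to carry, which is a change of 0 m. With 20% such losses the difference shrinks to 0.8 × 30 = 24 m. If 100 m is the SD of change and the placebo change is 0 m (both assumptions), power with all 480 is about 79%. The 87% with no loss needs the effect and SD unchanged.

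**The size is trivial.** Largely accepted. The trial randomises 480, so the relevant gap is 12 patients (2.4% of 492) and 0.9 percentage points of power. An SD of 98.9 m would remove it.

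**Conclusion.** The point holds as a minor arithmetic error. The stated 470 is not what the section's own formula and inputs give with a 20% dropout rate; that figure is 492. Rounding up to 480 recovers part of the difference. It leaves 79.1% power (78.9% by exact t) at a 20% loss of the week-12 outcome, and 80% power up to about 18% loss.

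These power figures assume an unadjusted comparison of means, 30 m as the between-group difference in change, 100 m as the SD of the analysed quantity, α = 0.025 one-sided (two-sided 5%), and equal proportional loss in both arms.

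A reader might infer that 480 cannot deliver 80% power under any planned analysis, or that the trial is materially underpowered. The document does not support either. The shortfall is under one percentage point, it is conditional on the assumptions above, and late dropout or baseline adjustment could remove it.

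**What to change.** Keep 480 and correct the paragraph, for example:

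> 393 evaluable participants are required; allowing for 20% dropout this is 492. The trial randomises 480 (320:160), which gives about 79% power at 20% loss of the week-12 outcome, or 80% power at up to 18% loss, for an unadjusted comparison.

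A power figure for the covariance analysis may be added. It should state the assumed correlation and the assumption that 100 m is the SD of change.

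The cost is a few lines of text and a stated power about one point lower. No patients, visits or analyses change.

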### Trial Completion

The trial will end once 480 patients have been randomized and all patients have completed 52 weeks of treatment and follow-up.

### Statistical Analyses

The statistical analysis plan will be specified before data analyses. The statistical analyses will be undertaken *via* Statistical Analysis System v9.4 (or higher version) by the Department of Medical Statistics, Peking University First Hospital. Professional statisticians who are independent of all other processes of our study will carry out analyses. Consistent with the CONSORT statement and ITT principle, and the last observation, carried forward method will be used for missing values. Cases in the per protocol set (PPS) will be those who adhere to the protocol closely without the absence of baseline characteristics. Analyses of primary outcome and curative effect will be carried out using a full-analysis-set approach and PPS approach. The safety analysis set will include all randomized patients who have accomplished at least one study visit. Participating centers will be required to sum-up participant numbers in each center and list participants who have been removed from PPS.

For continuous variables, we will calculate the mean, SD, median, minimum, maximum, and interquartile range. For categorical variables, we will describe various frequencies or percentages. The chi-square test or Fisher's exact test will be used for categorical variables. The Student's *t*-test will be used for continuous variables with a normal distribution. For data that do not have a normal distribution, intragroup or intergroup differences before and after treatment will be analyzed by the Wilcoxon rank-sum test. The proportion of patients with AEs in two groups will be compared using the chi-square test or Fisher's exact test. Because patients who had use of ARNIs before the recruitment may constitute a specific population, we will run sensitivity analyses of the outcomes with patients used ARNIs as basic treatment, and adjusted for the effect of ARNIs. Significance will be assumed at a two-sided *p*-value less than 5%. The relative risk with corresponding 95% confidence interval to compare dichotomous variables will be calculated. Table 6 shows the method of analysis for specific outcomes.

**TABLE 6 T6:** Outcomes and methods of analyses.

Outcome/variable	Hypothesis	Measures	Methods of analyses
Baseline balance test			
		Quantitative outcomes (age, temperature, heart rate, respiratory rate, and blood pressure)	*t*-test/Wilcoxon rank-sum test
		Qualitative outcomes (sex, marriage, and previous treatment)	Chi-squared test/Fisher’s exact test/rank-sum test
Adherence at post-intervention		Percent and cases of adherence <80% and ≥80%	Chi-squared test/Fisher’s exact test
Concomitant treatments		Percent and cases of concomitant treatments	Chi-squared test/Fisher’s exact test
Primary outcome			
6MWD	Improvement occurred		*t*-test/Wilcoxon rank-sum test
			Covariance analysis
Secondary outcomes			
NT-proBNP	Improvement occurred		*t*-test/Wilcoxon rank-sum test
NYHA classification	Improvement occurred		Wilcoxon rank-sum test
MLHFQ	Improvement occurred	Questionnaire	*t*-test/Wilcoxon rank-sum test
Echocardiographic parameters	Improvement occurred	Left ventricular end-diastolic diameter and LVEF	*t*-test/Wilcoxon rank-sum test
Clinical endpoint events	Improvement occurred	Clinical-endpoint event rate	Log-rank test
Safety outcomes			
AEs, SAE		Percent and cases of AEs and SAEs	Chi-squared test/Fisher’s exact test
Vital signs		Change value relative to baseline	*t*-test/Wilcoxon rank-sum test

6MWD, 6-min walk distance; NT-proBNP: N-terminal pro-B-type natriuretic peptide; NYHA, New York Heart Association; MLHFQ, Minnesota Living with Heart Failure Questionnaire; LVEF: left ventricular ejection fraction; AE, adverse event; SAE: serious adverse events.

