### Criteria for Withdrawal, Removal, Dropout, and Termination

The withdrawal criteria will be 1) exacerbation or deterioration that is clearly related to intake of the study drug; 2) an allergic reaction that is clearly associated with the study drug; 3) comorbidities, complications, adverse events (AEs), or serious adverse events (SAEs) during the trial, such as the necessity of long-term intravenous medication, repeated hospitalization for heart failure, or New York Heart Association (NYHA) class-IV symptoms; 4) the use of forbidden drugs or receipt of prohibited treatment affect the measures of efficacy and safety; 5) poor compliance by participants, or the amount of drug used does not meet the regulations (<80% or >120%); 6) participants request to withdraw from the study; 7) the blinding is uncovered or emergency unblinding is required.

Participants who fail to complete the observational period proposed in the trial, regardless of time and reasons, will be considered to be “dropout” cases. Reasons for dropout will be recorded in electronic case report forms (eCRFs), and the last data recorded will be included in data analyses. During the trial, a participant may be removed if he/she 1) is included mistakenly due to a misdiagnosis, 2) has not taken medication after study inclusion, 3) is participating in other clinical trials, and 4) has incomplete data and no evaluable records after inclusion. Another reason for removal is if the combined use of drugs has a great influence on the efficacy and safety of the study drug. Removal cases will not be included in analyses of the intention-to-treat (ITT) population.

The entire research study will be terminated if 1) there is a poor clinical effect of the test drug, and there is no need to continue the trial; 2) there are major defects in the trial; and 3) administrative authorities terminate the trial.

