### Interventions

Eligible participants will be allocated randomly to the GXST group or placebo group. If GXST have been used before randomized, a 2-week drug washout period should be implemented to avoid any potential complication from GXST. All participants will receive standard treatment.

The GXST group will receive GXST (batch number: 190214, 0.3 g per capsule, op, 3 capsules per time, thrice daily). The placebo group will receive capsule stimulants (batch number: 190215, 0.3 g per capsule, op, 3 capsules per time, thrice daily).

Concerning standard treatment, during the intervention period, according to the guidelines for CHF treatment (Ponikowski et al., 2016; Chinese Society of Cardiology and Chinese Medical Doctor Association, 2018), ACEIs, and/or angiotensin receptor blockers, β-blockers, aldosterone receptor blockers, or diuretics should be used. TCM formulations with a similar composition and efficacy to those of GXST will not be allowed to be used. Concomitant treatments for comorbidities (e.g., hypertension, diabetes mellitus, hyperlipidemia, and other chronic conditions) are permitted during the intervention. Researchers should record the concomitant medication truthfully and maintain dose stability during the trial.

Concerning emergency treatment, in the event of an SAE or acute exacerbation of the disease during treatment (e.g., acute heart failure and acute coronary syndrome), participants should be treated first, and the treatment status should be recorded as an AE record form and combined medication record form. If the participant's condition deteriorates during treatment and it is not advisable to continue the trial (e.g., long-term intravenous medication, repeated heart failure that necessitates hospital admission, or NYHA class-IV symptoms), one should consider terminating the trial and switching to surgery or another type of clinical treatment. Patients will be classified in the analysis as “treatment ineffective.”

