## Outcomes

### Primary and Secondary Outcomes

The details of items to be measured and the time window of data collection are shown in Table 5. The primary outcome is the improvement in 6-min walk distance (6MWD) (Holland et al., 2014). 6MWD will be measured within 24 h after enrollment and 12 weeks after treatment to evaluate the change in exercise tolerance. Improvement will be calculated using the following formula:

**TABLE 5 T5:** Study schedule.

Study phase time	Baseline period	Intervention period			Follow-up
	Visit 1	Visit 2	Visit 3	Visit 4	Every 4 weeks
	−7 to 0 days	4 weeks	8 weeks	12 weeks	Until 52 weeks
Data collection at baseline					
Informed consent	×				
Inclusion/exclusion criteria	×				
Demographic data	×				
Obtain the central random number	×				
Previous history, medical history, and allergies	×				
Comorbidities and co-medications	×				
Safety evaluation					
Vital signs	×	×	×	×	
Physical examination	×	×	×	×	
Blood routine	×			×	
Urine routine	×			×	
Blood biochemistry	×			×	
Myocardial zymogram and troponin	×			×	
ECG	×			×	
Chest radiograph or CT	×			×	
Urine pregnancy test	×			×	
Efficiency evaluation					
6MWD	×			×	
NT-proBNP	×			×	
NYHA class	×	×	×	×	
MLHFQscore	×	×	×	×	
Echocardiographic parameters	×			×	
Clinical-endpoint events		×	×	×	×
Other work					
Dispense drug	×	×	×		
Recovery and record of study drug		×	×	×	
Metabolomics and proteomics	×			×	
Record AEs		×	×	×	×
Complications due to medications		×	×	×	
Evaluate compliance		×	×	×	×

CT, computed tomography; 6MWD, 6-min walk distance; NYHA, New York Heart Association; MLHFQ, Minnesota Living with Heart Failure Questionnaire; TCM, traditional Chinese medicine; AE, adverse event.

Improvement in exercise tolerance = 6MWD value after treatment − 6MWD value before treatment

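### With 6MWD measured only at baseline and week 12, LOCF scores every analysed patient lacking a week-12 walk as exactly 0 m change

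*Protocol article*

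**What the plan says.** All places are in the protocol article.

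- **Statistical Analyses** names one method for missing data: "the last observation, carried forward method will be used for missing values". No outcome is exempted. The primary outcome is analysed in the full analysis set and the per-protocol set. The only sensitivity analysis named concerns ARNI use.
- **Criteria for Withdrawal, Removal, Dropout, and Termination** takes the same line for dropouts: "the last data recorded will be included in data analyses". A dropout is defined broadly: "Participants who fail to complete the observational period proposed in the trial, regardless of time and reasons". Removed cases are treated differently: "Removal cases will not be included in analyses of the intention-to-treat (ITT) population".
- **Primary and Secondary Outcomes** fixes the timing: "6MWD will be measured within 24 h after enrollment and 12 weeks after treatment". Table 5 marks 6MWD at Visits 1 and 4 only, and no walk at early withdrawal is mentioned. The variable is a difference: "Improvement in exercise tolerance = 6MWD value after treatment − 6MWD value before treatment".
- **Interventions** covers patients who deteriorate so far that continuing is inadvisable: "Patients will be classified in the analysis as" treatment ineffective. No outcome in the article uses that class.
- **Sample Size** gives the planning values: "we assumed that the improvement in 6MWD is 30 m, and the combined standard deviation (SD) is 100 m in the present study", with an allowance of 20% for dropout.

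**The concern.** LOCF presupposes an intermediate measurement to carry forward. Here there is none, so the rule becomes baseline carried forward and the change is a constant 0 m.

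The patients concerned are unlikely to be a random subset. The withdrawal criteria include NYHA class IV symptoms, repeated heart-failure admission, poor compliance and unblinding. Where such patients have no week-12 walk, those who got worse are recorded as unchanged, as is anyone who died before week 12. Patients who left while improving lose their gain.

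Two things are at stake in the trial's single primary result. The estimate comes to depend on how many patients each arm loses. Constants entered as observations also shrink the variance, so the interval claims precision that the data do not have.

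**Working it through.** **Inputs from the article.** Difference 30 m, SD 100 m, power 80%, alpha 0.025, dropout 20%, allocation 320 to GXST and 160 to placebo.

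**The plan's own figure.** With k = 2, the smaller arm is [(1.960 + 0.842) × 100 / 30]² × 1.5 = 130.8, so the total is 3 × 130.8 = 392.4. Multiplying by 1.2 gives 470.9, which reproduces the stated 470. Alpha 0.025 therefore acts as one-sided, equivalent to the two-sided 5% used in the analysis. The 20% is thus the plan's own allowance for loss to the 6MWD analysis.

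**How many patients.** 0.20 × 480 = 96 if all dropout precedes week 12, leaving 384 walks (256 + 128). If half does, 48 are affected and 432 walks remain (288 + 144).

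**Formulas.** Let m be an arm's true mean change and d its proportion missing.

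- Arm mean under LOCF: (1 − d)m
- Arm variance under LOCF: (1 − d) × 100² + d(1 − d)m²
- SE from observed walks only: 100 × √[1/(320(1 − d)) + 1/(160(1 − d))]

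The article gives no mean change by arm, so placebo is varied from 0 to 40 m with GXST 30 m higher. Missing patients are taken to be like completers.

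**Equal 20% missing**

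- Effect: 0.8 × 30 = 24 m.
- LOCF SE, means 30 and 0: √[(8000 + 0.16 × 900)/320 + 8000/160] = √(25.45 + 50.00) = 8.69 m.
- LOCF SE, means 70 and 40: √[(8000 + 0.16 × 4900)/320 + (8000 + 0.16 × 1600)/160] = √(27.45 + 51.60) = 8.89 m.
- Observed-data SE: 100 × √(1/256 + 1/128) = 10.83 m. The ratio is 0.80 to 0.82, so the interval is about 18-20% too narrow.
- With all 480 walks observed the SE would be 100 × √(1/320 + 1/160) = 9.68 m. LOCF with a fifth of the data missing therefore claims more precision than complete data would give.
- With means 50 and 20, the nominal 95% interval covers 30 m about 89-90% of the time.

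**Equal 10% missing**

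- Effect: 0.9 × 30 = 27 m.
- LOCF SE, means 30 and 0: √[(9000 + 0.09 × 900)/320 + 9000/160] = 9.20 m, against 100 × √(1/288 + 1/144) = 10.21 m. The ratio is 0.90, so the interval is about 10% too narrow.

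**Unequal missingness.** Splits and means are assumed. Every row has 96 of 480 missing.

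| Mean change, GXST / placebo (m) | Missing, GXST / placebo | True difference (m) | LOCF difference (m) | Consequence |
|---|---|---|---|---|
| 50 / 20 | 22.5% / 15% | 30 | 38.75 − 17 = 21.75 | coverage 85% |
| 30 / 30 | 20% / 20% | 0 | 0 | type I error 5% |
| 30 / 30 | 15% / 30% | 0 | 25.5 − 21 = +4.5 | type I error 7.5-8.3% |
| 50 / 50 | 15% / 30% | 0 | 42.5 − 35 = +7.5 | type I error 13-14% |
| 30 / 30 | 25% / 10% | 0 | 22.5 − 27 = −4.5 | type I error 7.9% |
| completers 50 / 20, missing −50 | 25% / 10% | 25 − 13 = 12 | 37.5 − 18 = 19.5 | overstated by 7.5 m |

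Type I error is two-sided. Where a range is shown, it spans a simulation with the pooled t-test (20,000 trials) and the normal approximation. These figures are for the unadjusted difference in change. The covariance analysis in Table 6 would alter the SEs by an amount that depends on the correlation of baseline with week 12, which the article does not give.

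**The case against.** Several points on the other side stand.

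- **Not every dropout is scored zero.** A reader might infer that all 96 expected dropouts become zeros. Dropout runs over the whole observation period to week 52, so a patient lost after week 12 keeps a measured change. Removed cases leave the ITT set and are not imputed. At the planned rate, 96 is an upper bound.
- **Power is not the harm.** With equal missingness the estimate and SE shrink together: 24/8.69 = 2.76 against 30/10.83 = 2.77. Power is 77-79% under LOCF and 79% from observed walks. With no effect and equal missingness, type I error stays at 5%.
- **The direction of bias is not fixed.** One might read the rule as conservative, or as favouring GXST. The table shows both directions, and every unequal scenario rests on assumed inputs.
- **No flat contradiction with the treatment-ineffective class.** Zero change can be read as no improvement, and Statistical Analyses mentions curative effect separately from the primary outcome, so the class may belong there. What remains is a gap: the class has no value in metres, while the dropout and LOCF rules apply to the same patients.
- **A completer analysis is no cure.** Suppose 20% of placebo and 10% of GXST patients worsen by 60 m, the rest gain 30 m, and exactly the worsening patients are missing. The true difference is 21 − 12 = 9 m. LOCF gives 27 − 24 = 3 m and completers give 0 m. Observed walks serve above only as a benchmark for precision.

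The per-protocol analysis does not test the missing-data assumption. An unseen SAP does not remove the point either, because the article positively fixes LOCF.

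**Conclusion.** The point holds for analysed patients without a week-12 6MWD. For them LOCF is baseline carried forward, and the primary value is fixed at 0 m whatever happened to the patient. That follows from the text and needs no assumption.

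The size does need assumptions. The shrinkage to 24 m (20% missing) or 27 m (10%), and the narrowing of the interval by about 18-20% or 10%, rest on equal missingness, an SD of 100 m and missing patients resembling completers. The false-positive rates rest on assumed dropout splits and arm means. They show that type I error can exceed 5%, not that it will. The documents do not support stronger claims about all dropouts, a one-directional bias, lost power or contradictory rules.

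Because the rule governs the primary result and is simple to change, it should be changed before unblinding.

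**What to change.** Before unblinding, amend the protocol or SAP for the primary outcome:

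1. Replace LOCF with multiple imputation of week-12 6MWD, done by arm, using baseline 6MWD, centre, and NYHA class and MLHFQ score at the scheduled visits. Table 5 already collects both at baseline and weeks 4, 8 and 12. Follow with the planned covariance analysis. Reason for stopping can be added as a predictor only if some patients who stopped still have a week-12 walk.
2. State how deaths and patients stopped for worsening are handled on the primary scale, and reconcile the sections on withdrawal and dropout, Interventions and Statistical Analyses for these patients. One option is a prespecified unfavourable imputed value, acknowledging that it changes what is estimated. Another is a separate rank-based analysis; worst-rank scores have no value in metres and cannot enter the covariance analysis.
3. Add a delta-adjusted sensitivity analysis that shifts the imputed values, separately by arm, until the conclusion changes. This matters because imputation from observed data alone may not capture unrecorded worsening.

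The cost is wording, modest programming and honestly wider intervals. If all 20% is lost before week 12, the 95% half-width goes from about 17 m (1.96 × 8.7 to 8.9) towards 21 m (1.96 × 10.83), less whatever the auxiliary measurements recover. No new data collection is needed.
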